### Methods for additional analyses {20b}

There are no subgroup analyses and adjusted analyses planned.

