### Trial design {8}

This is a multi-center, prospective, open-label, randomized study to compare the efficacy of baricitinib + hydroxychloroquine (HCQ) with HCQ alone in pSS patients. Patients will be randomized (2:1) to receive baricitinib 4 mg per day + HCQ 400 mg per day or HCQ 400 mg per day alone. We will switch HCQ to baricitinib + HCQ if the patient in the latter group has no response at week 12. The final evaluation will be at week 24.

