### Eligibility criteria {10}

#### Inclusion criteria

Must read and understand the informed consent approved by the institutional review board (IRB)/ethics review board (ERB) governing the site and provide written informed consent.Stated willingness to comply with all study procedures and availability for the duration of the study.Ability to take oral medication and be willing to adhere to the study intervention regimen.Male or female, aged between 18 and 75 years.Fulfill the 2016 ACR/EULAR classification criteria for pSS [19].With moderate activity (ESSDAI ≥ 5) on HCQ 400 mg per day treatment for at least 12 weeks at the screening visit.With serological activity defined as hypocompleminemia or elevated C-reactive protein (CRP)/erythrocyte sedimentation rate (ESR)/immunoglobulin G (IgG) /rheumatoid factor (RF) level (excluding acute and chronic infection and other factors).Nonpregnant, nonbreastfeeding female patient.Males with potential for reproduction must agree to practice effective birth control methods described above too.

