### Outcomes {12}

#### Primary outcome measure

The rate of ESSDAI response, or MCII of ESSDAI, which was defined as an improvement of ESSDAI at least three points, at 12 weeks.

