## Assignment of interventions: allocation

### Sequence generation {16a}

Eligible participants will be randomized into HCQ group or baricitinib + HCQ group with a computer-generated randomization schedule operated at the application of CRDC.

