## Statistical methods

### Statistical methods for primary and secondary outcomes {20a}

Data will be analyzed using IBM SPSS 23.0 (Chicago, IL, USA). Differences will be considered statistically significant if *p* < 0.05. Continuous variables were analyzed using paired *t*-tests for data comparison between the two treatment groups. Categorical variables were analyzed using the chi-square test or Fisher’s exact test, where appropriate. Two-tailed tests were used for all analyses, and *P* < 0.05 was considered statistically significant. The 95% confidence interval of the fixed effect size will be used to assess whether treatment difference reaches the minimally clinical important difference. The changes in outcome measures among all participants at 24 weeks will be used for intention-to-treat analyses.

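### No baseline-adjusted analysis is planned although ESSDAI is measured before treatment in every patient: a possible loss of precision, not a bias

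*Protocol article*

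**What the plan says.** Methods for additional analyses {20b} states: "There are no subgroup analyses and adjusted analyses planned". This is a stated decision and not an item left open for the analysis plan.

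Statistical methods for primary and secondary outcomes {20a} agrees with it. For binary outcomes: "Categorical variables were analyzed using the chi-square test or Fisher’s exact test, where appropriate". For continuous outcomes: "Continuous variables were analyzed using paired *t*-tests for data comparison between the two treatment groups". No covariate appears in either.

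The primary outcome is ESSDAI response, "which was defined as an improvement of ESSDAI at least three points, at 12 weeks". The entry criterion is "With moderate activity (ESSDAI ≥ 5) on HCQ 400 mg per day treatment for at least 12 weeks at the screening visit", and no upper limit is given. Table 2 in Participant timeline {13} schedules ESSDAI at screening, week 0, week 12 and week 24. Allocation is 2:1, and Sequence generation {16a} describes a computer-generated schedule without naming a stratification factor.

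**The concern.** Response is an absolute fall of three points from a starting score that varies between patients. A patient who starts at 5 must lose 3/5 = 60% of the score to respond; one who starts at 15 must lose 3/15 = 20%. The starting score is part of the endpoint's own definition, so it is the natural candidate for a prognostic covariate, and it is already scheduled for everyone.

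If baseline ESSDAI does predict response, an unadjusted comparison gives a wider interval than the same data allow, and nothing in the design or analysis as described takes account of a chance difference in baseline between arms. The same holds for the change-from-baseline secondary outcomes (PGA, serology, gland function, focus score). Timing matters as well. The trial is open label, so adjustment added after an imbalance has been seen would be post hoc and would contradict {20b}.

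**Working it through.** **Inputs from the document.** Response 70% v 30%, 46:23 evaluable, 20% dropout, 58:29 enrolled (Sample size {14}); two-sided 5% tests ({20a}).

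**Assumed, because the document does not give them.** Prognostic strength of baseline ESSDAI: log-odds ratio 0 to 1.5 per SD. Baseline–follow-up correlation rho of continuous outcomes: 0.3 to 0.7, with equal variances.

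**1. The plan's own figures.** The dropout step reproduces: 46/0.8 = 57.5, so 58; 23/0.8 = 28.75, so 29; total 87. The evaluable number does not follow from 80% power: the usual two-proportion formula at 2:1 gives 18 controls (54 in total), or 21 (63) with continuity correction, and 23 controls correspond to 90% power. That is a separate matter. Here 46:23 and 58:29 are simply taken as the sizes.

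**2. Unadjusted precision.** SE of the risk difference at 46:23 = sqrt(0.21/23 + 0.21/46) = 0.117, so the 95% CI half-width is 1.96 × 0.117 = 22.9 points. Power is 90.3% at 46:23 and 95.7% at 58:29.

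**3. Chance imbalance in baseline, in SD units.**
- At 46:23: SE = sqrt(1/46 + 1/23) = 0.255; an imbalance above 0.25 SD has probability 33%, above 0.5 SD 5%.
- At 58:29: SE = sqrt(1/58 + 1/29) = 0.227; the probabilities are 27% and 3%.

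**4. Adjustment for the primary endpoint.** Simulation with 3,000 trials per row at 46:23. Response follows a logistic model in arm and a standard normal baseline, with marginal rates held at the stated values. The raw risk difference is compared with the standardised risk difference from logistic regression. R² is the share of response variance that baseline explains.

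| Log-OR per SD | R² | Variance ratio, adjusted/raw (70% v 30%) | Power raw → adjusted (70% v 30%) | Power raw → adjusted (60% v 30%) |
|---|---|---|---|---|
| 0 | 0 | 1.02 | 0.90 → 0.90 | 0.67 → 0.67 |
| 0.5 | 0.05 | 0.97 | 0.90 → 0.92 | 0.67 → 0.71 |
| 1.0 | 0.16 | 0.86 | 0.90 → 0.94 | 0.68 → 0.76 |
| 1.5 | 0.27 | 0.78 | 0.90 → 0.96 | 0.67 → 0.81 |

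Simulations of the three non-zero rows at 70% v 30% with 1,000 and 6,000 trials gave variance ratios of 0.97, 0.89, 0.74 and 0.97, 0.86, 0.76. The strongest setting therefore cuts the variance by 22% to 26%. By the approximation SE × sqrt(1 − R²), the half-width falls from 22.9 points to 21.8 at R² 0.10, 20.5 at 0.20 and 19.2 at 0.30.

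**5. Continuous outcomes.** A paired t-test cannot compare two independent groups, so the nearest workable reading of {20a} is a two-sample comparison of change scores. With equal variances, the ratio of ANCOVA to change-score variance is (1 − rho²)/(2(1 − rho)) = (1 + rho)/2, which is 0.65, 0.75 and 0.85 at rho 0.3, 0.5 and 0.7.

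**The case against.** The strongest reply is that nothing here is invalid. A chi-square or Fisher test of a randomised binary endpoint keeps its type I error, and its confidence interval already allows for chance imbalance. A reader might infer that the unadjusted result is biased, or that imbalance would pass for a drug effect. The documents do not support that: the imbalance is ordinary sampling error. Its likely effect is also modest. At 58:29, one SE of imbalance at a log-odds ratio of 0.5 moves the risk difference by about 0.227 × 0.5 × 0.21 = 2.4 points (4.8 at 1.0), against a half-width of 1.96 × sqrt(0.21/58 + 0.21/29) = 20.4 points. All of this stands.

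A reader might also infer that baseline must be prognostic because it limits how far a patient can improve. That does not follow. A patient who enters at 5 can still fall by three points, and patients with high scores may be harder to treat. The document reports no association between baseline and response. This stands too, and it is why the range has to include zero, where adjustment gains nothing and costs about 2% in variance.

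Third, at 70% v 30% the unadjusted test already has about 90% power. The gain therefore matters mainly if the true effect is smaller, and for the continuous outcomes.

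The reply does not show that the omission is harmless in general. The covariate is already scheduled, the possible loss is negligible and the possible gain is material.

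**Conclusion.** The point holds as one of efficiency and robustness. {20b} declines adjustment, {20a} offers only unadjusted tests, and the obvious covariate is measured before treatment in every patient. For the primary risk difference at 46:23 and 70% v 30%, adjustment changes the variance by between about +2% and about -25% over the assumed log-odds ratios of 0 to 1.5 per SD. For continuous outcomes, ANCOVA has 65% to 85% of the change-score variance under the assumed correlations and equal variances. Where in these ranges the trial lies cannot be told from the document.

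The sentence in {20a} that "The 95% confidence interval of the fixed effect size will be used to assess whether treatment difference reaches the minimally clinical important difference" should not be read as a planned adjusted model, since no such model is described. Its unclear wording is a separate defect and adds no weight here.

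**What to change.** Before any outcome is compared by arm, replace the part of {20b} on adjusted analyses (the statement on subgroups can stay) and bring {20a} into line:

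> Week-12 ESSDAI response will be analysed by logistic regression on randomised arm and week-0 ESSDAI, reported as a standardised risk difference with a 95% CI (delta method or bootstrap), with the unadjusted chi-square or Fisher test as supportive. Continuous outcomes will be compared between arms by ANCOVA with the baseline value as covariate, in place of paired t-tests.

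Three details need fixing with it:
- Choose either the delta method or the bootstrap in advance.
- Name the baseline visit. Table 2 has ESSDAI, ESSPRI, PGA, ESR and CRP at both screening and week 0, but immunoglobulins, complement, RF, gland function and biopsy at screening only. The same ESSDAI visit should serve as covariate and as the reference for the three-point fall.
- Report the standardised risk difference and not the conditional odds ratio, so that the adjusted and supportive analyses estimate the same quantity.

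The cost is a wording change and slightly more analysis work, with no new data and a negligible loss of precision if baseline proves not to be prognostic.

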### Interim analyses {21b}

Patients who have no ESSDAI response to HCQ treatment alone at week 12 will be switched to baricitinib + HCQ group and added on with baricitinib 4 mg per day until the end of the study (week 24). There are no interim safety analyses planned for this trial.

### Methods in analysis to handle protocol non-adherence and any statistical methods to handle missing data {20c}

No imputation of missing data will be considered for the efficacy and analysis in this trial.

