### Sample size {14}

According to the results of our pilot study [24] and clinical experiments, the expected response rate is 70% (μ) in baricitinib + HCQ group, and 30% (μ0) in HCQ group. We use this formula to calculate the sample size:$$N=\frac{{\left({z}_{a/2}+{z}_{\beta }\right)}^{2}{\sigma }^{2}}{{\left(\mu -{\mu }_{0}\right)}^{2}}$$

Zα/2 = 1.96 when alpha = 0.05, Zβ = 0.84 when beta = 0.2. After calculation, the sample will be 46:23. And consider the dropout rate as 20%, we will involve approximately 87 patients (58:29) for the study.

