### Adverse event reporting and harms {22}

An adverse event (AE) is any untoward medical occurrence (including an abnormal laboratory finding), in a patient or clinical trial subject administered a medicinal product temporally associated with the use of a study agent(s), whether or not related to the study agent(s), occurring as soon as the patient has signed the informed consent form and at any time during the study. All adverse events reported by the subject or observed by the investigators will be recorded in the CRF. AEs also include an undesirable medical condition occurring, even if no study treatment has been administered.

For all AEs, the investigator will assess the causal relationship between the study drug and the AE using his/her clinical expertise and judgment according to the following algorithm that best fits the circumstances of the AE:

The investigator will interpret and document whether or not an AE has a reasonable possibility of being related to study treatment, study device, or a study procedure, taking into account the disease, concomitant treatment or pathologies. The investigator will decide whether the patient will drop out of the study due to the AEs.

A “reasonable possibility” means that there is a cause and effect relationship between the investigational product, study device, and study procedure and the AE. The investigator answers yes/no when making this assessment.

A serious AE (SAE) is any AE from this study that results in one of the following outcomes: death; initial or prolonged inpatient hospitalization; a life-threatening experience (that is, immediate risk of dying); persistent or significant disability/incapacity; congenital anomaly/birth defect; important medical events that may not be immediately life-threatening or result in death or hospitalization but may jeopardize the patient or may require intervention to prevent one of the other outcomes listed in the definition above.

Record the incidence of AEs and SAEs, especially which may cause discontinuation of the study.

Attention should be paid to monitoring the risk of serious infections such as tuberculosis, hepatitis B and other infections after medication. The risk of thromboembolic events should be monitored. Other adverse events included abnormal blood routine test, abnormal liver and kidney function test, allergic reaction, and gastrointestinal reaction.

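### With imputation ruled out and no outcome assigned to a missing week-12 ESSDAI, the primary test covers only observed patients (about 69 of 87) and can be biased in either direction

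*Protocol article*

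**What the plan says.** - **Endpoint.** Section {12} defines it so: "The rate of ESSDAI response, or MCII of ESSDAI, which was defined as an improvement of ESSDAI at least three points, at 12 weeks".
- **Test.** Section {20a} names the chi-square or the Fisher test for categorical data, and adds: "Two-tailed tests were used for all analyses". Section {20b} plans no adjusted analysis.
- **Missing data.** Section {20c}: "No imputation of missing data will be considered for the efficacy and analysis in this trial".
- **Analysis set.** Section {20a}: "The changes in outcome measures among all participants at 24 weeks will be used for intention-to-treat analyses". This is the only mention of intention-to-treat, and it concerns week 24.
- **Expected loss.** Sample size {14} asks the reader to "consider the dropout rate as 20" per cent and raises 46:23 to 58:29.
- **Who leaves.** Section {22}: "The investigator will decide whether the patient will drop out of the study due to the AEs". Section {17a} says that nobody is blinded.
- **Data after leaving.** Section {18b} ends data collection when a participant withdraws both from the study and from further disclosure of information.

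**The concern.** A two-by-two table needs an outcome for every patient in it. Table 2 schedules post-baseline ESSDAI only at weeks 12 and 24, so a patient lost before week 12 has no earlier post-baseline score to draw on. No longitudinal model is planned that could use partial data. With imputation excluded, such a patient leaves both numerator and denominator, and the comparison is no longer between the groups as randomised.

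This is a rule the article states, not a detail left to an analysis plan: a later plan that counted missing scores as non-response would contradict it. At stake is the validity of the primary comparison in a small unblinded trial, where investigators who know the allocation decide on dropout for adverse events.

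**Working it through.** **1. The plan's own figure.** Sample size {14} starts from 46:23 evaluable patients with 20% dropout.

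- 46/0.8 = 57.5, so 58
- 23/0.8 = 28.75, so 29
- total 58 + 29 = 87

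The dropout step reproduces. It treats dropouts as lost to the analysis: 87 − 69 = 18 patients (12 and 6) are not in the primary test. Whether 46:23 follows from the stated power is a separate question that does not affect this point.

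**2. Bounds without a dropout model.** Suppose the planned 70% v 30% is observed in 46:23, so that 12 and 6 patients are unknown.

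- Lowest difference in all randomised: 0.7×46/58 − (0.3×23 + 6)/29 = 0.555 − 0.445 = 11 points
- Highest: (0.7×46 + 12)/58 − 0.3×23/29 = 0.762 − 0.238 = 52 points

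An observed 40 points is compatible with anything from 11 to 52.

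**3. Bias when non-responders leave at different rates.** Assumptions, not in the documents: true response p = 0.40 in both arms, only non-responders leave, and a fraction d of them is lost. The observed-case rate is p / [p + (1 − p)(1 − d)] and total dropout in an arm is (1 − p)d. Type I error is simulated at 58:29 with the two-sided chi-square test.

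| Non-responder loss, baricitinib + HCQ v HCQ | Total dropout by arm | Observed-case rates | Bias (points) | Type I error |
|---|---|---|---|---|
| 33% v 33% | 20% v 20% | 50% v 50% | 0 | about 5% |
| 40% v 20% | 24% v 12% | 52.6% v 45.5% | +7 | about 9% |
| 45% v 10% | 27% v 6% | 54.8% v 42.6% | +12 | about 17% |
| 25% v 50% | 15% v 30% | 47.1% v 57.1% | −10 | about 12% |

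Example, third row: 0.40/(0.40 + 0.60×0.55) = 0.548 and 0.40/(0.40 + 0.60×0.90) = 0.426. Overall dropout is about 20% in every row, for example (2×27 + 6)/3 = 20.

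**4. Equal dropout totals do not remove the risk.** Assume true response of 30% in both arms and 20% dropout in each. If the baricitinib losses are all non-responders and the HCQ losses are random, the observed rates are 0.30/0.80 = 37.5% v 30%. That is a bias of +7.5 points, and the exact type I error at 46:23 is 9.0% against 5.2% without bias. Reversing the pattern gives −7.5 points and 10.2%.

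**5. Power if missing counts as non-response (58:29, true 70% v 30%).**

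- 20% dropout in each arm, unrelated to response: 0.7×0.8 = 56% v 0.3×0.8 = 24%. Exact power is 84.6% (chi-square) or 80.4% (Fisher).
- 27% v 6% dropout, unrelated to response: 0.7×0.73 = 51% v 0.3×0.94 = 28%. Power is about 56% (chi-square) or 49% (Fisher).
- The same dropout with no effect (40% in both arms): 29.2% v 37.6%, a bias of −8.4 points, with 13.5% rejection by chi-square.

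**The case against.** Several stronger readings are tempting, and the documents do not support them.

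- **That the rule overstates the benefit of baricitinib.** The article gives no dropout by arm. Controls might stay for the week-12 switch, but they might equally leave an open-label arm that continues the drug on which their disease was already active. The sign is unknown, and the bias is zero if loss is unrelated to response within each arm. The 45% v 10% row is one chosen scenario, not an expectation.
- **That patients stopped by the laboratory, HBV, TB or VTE rules are deleted.** Those rules stop the investigational product, not follow-up. Such a patient can still have a week-12 ESSDAI, and section {20c} does not remove it. Only the sentence in {22} on study dropout for adverse events links toxicity directly to missing data.
- **That the primary analysis flatly contradicts a stated intention-to-treat plan.** The phrase "among all participants at 24 weeks will be used for intention-to-treat analyses" concerns week 24. For week 12 the article names no analysis set.
- **That dropouts are failures, so 56% v 24% is the true result.** If loss is unrelated to response, the observed 40 points are unbiased and the 32 points are attenuated.

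What stands on the other side: counting missing scores as non-response is no neutral cure, as step 5 shows. It does not follow that the present rule is adequate. That rule leaves about a fifth of the randomised patients out of the primary test and provides no analysis of how much this matters.

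**Conclusion.** The concern holds in a conditional form. As written, the primary test is an observed-case analysis of about 69 of 87 patients, where observed means having a week-12 ESSDAI, not finishing week 24. This does not fit an intention-to-treat analysis. Bias arises if loss depends on response differently in the two arms. Over the scenarios in step 3 it runs from −10 to +12 points, with a type I error of about 5% to 17%. These figures rest on an assumed 40% response in both arms and on only non-responders leaving. The 20% is the plan's own allowance, which it does not divide by arm or by time. Because both direction and size are unknown, this is a point that should be fixed, not evidence that the trial will favour baricitinib.

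**What to change.** Replace the sentence in section {20c} with:

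> All randomised patients are in the week-12 primary analysis by allocated arm. Observed week-12 ESSDAI is used whether or not study drug was stopped; a patient with no week-12 ESSDAI counts as a non-responder. Multiple imputation and a tipping-point analysis are sensitivity analyses.

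In section {18b}, state that the week-12 ESSDAI is still collected after study drug is stopped, unless the patient withdraws consent for data. This makes explicit what that section already largely implies. Patients who stop drug but have an observed score should not be recoded as non-responders: that would overwrite real data and change the primary endpoint, which is ESSDAI improvement alone.

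The cost is wording and a little programming. The reported response rates will be lower, and non-responder counting is itself biased when dropout unrelated to response differs by arm, so the sensitivity analyses are needed. The 80% power should be stated only with its condition of about 20% dropout in each arm.

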### Plans to give access to the full protocol, participant-level data, and statistical code {31c}

The full protocol, anonymous participant-level dataset, and statistical code of this study can be made available by the corresponding author upon reasonable request and according with the research collaboration agreement.

## Oversight and monitoring

### Composition of the coordinating center and trial steering committee {5d}

This is a multiple center study performed in eight different centers. The leading site is Peking Union Medical College hospital (PUMCH). Day to day support for the trial is provided by:Principle investigator: takes supervision of the trial and medical responsibility of the patients.Data manager: organizes data capture, safeguards quality and data.Study physician: identifies potential recruits, takes informed consent, ensures follow-up and safety monitor according to protocol.

There is no trial steering committee or stakeholder and public involvement group.

